#### Study End Points

##### Early Detection Cohort

We will assess effectiveness based on dual primary end points. The first primary end point is the proportion of those who complete a physical examination visit for KS and NHL and the proportion of those who are up to date with CC screening (female participants only) at 12 months. The second primary end point is the proportion of those who complete the recommended follow-up supplemental or diagnostic procedures (within 3 months of receiving follow-up referral), those who initiate cancer treatment (within 3 months of diagnosis), and those who complete additional cancer detection visits over 36 months. The secondary end point, evaluated at 36 months, is the proportion of those diagnosed at an early stage (among those diagnosed with KS, NHL, and CC). We will likely have a few cancer cases in the study facilities. Therefore, these findings will not be conclusive but will offer insights into the potential impact of the ARROW program on facilitating diagnosis at an early stage.

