#### Sample Size and Recruitment

##### Early Detection Cohort

We will use stratified random sampling to select an equal number of male and female participants and a mix of AYA living with HIV with perinatally and behaviorally acquired HIV. In terms of age distribution, 20% (720/3600) of the sample will be aged 15 to 19 years, 20% (720/3600) will be aged 20 to 24 years, and 60% (2160/3600) will be aged 25 to 39 years. We will oversample AYA living with HIV in each stratum to account for AYA living with HIV who may not meet inclusion criteria or who decline to participate. HIV facility staff will contact AYA living with HIV or consenting adults (for those aged 15 to 17 years) to discuss the study, and those interested will meet with trained data collectors who will assess eligibility and obtain consent or assent. The sample size was calculated assuming conventional specifications (α=.025 for each end point, 2-sided tests) based on the dual primary end points and allowing for the detection of an absolute 20% point improvement in the primary end points, which is our minimum threshold to consider the ARROW program successful. For the one-time education arm, given the current low level of uptake of early diagnosis services, we estimate uptake of physical examinations to be about 15% (15/100) and CC screening to be about 20% (20/100) at 12 months. With our proposed sample size of 3600, we will be able to detect a 20% difference in uptake of physician examination (35% in the ARROW arm) with over 90% power and CC screening (40% in the ARROW arm) with over 85% power. We can achieve this even after accounting for up to 10% attrition at 12 months (a previous study conducted by the research team achieved this retention rate without the level of active participant contact planned for this study) [67]. We estimate that the interclass correlation coefficient will be in the range of 0.03 to 0.05 because correlation coefficients for binary data are typically quite small, especially when physical examinations and screening uptake are very low [68].

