**Data elements for primary, secondary, and tertiary end points: HIV and cancer care continuum**				
	Proportion of participants completing physical examination (KS^a^ and NHL^b^) and up to date with CC^c^ screening	Confirmation of services will be based on clinical records and PC^d^ tracking tool (primary end point at 24 mo)	Biological, imaging, and clinical procedures identified through clinical records and study database	12, 24, and 36 mo
	Proportion of participants completing diagnostic tests and initiating treatment in ≤90 d	Measured as days from referral for testing and cancer diagnosis, respectively; based on chart review and study data	Biological, imaging, and clinical procedures identified through clinical records and study database	24 and 36 mo
	Proportion of participants completing repeat examinations and screening at the recommended interval	Screening every 2 y for CC and annual examination (especially when CD4^e^<100) based on the Zambian guidelines	Biological, imaging, and clinical procedures identified through clinical records and study database	36 mo
	Proportion of participants with early-stage diagnosis^f^	Stage 1 or 2 for NHL and CC; good risk for KS^g^	Biological, imaging, and clinical procedures identified through clinical records and study database	36 mo
	Proportion of participants adherent to cancer treatment^f^	Complete cancer treatment modalities as recommended	Biological, imaging, and clinical procedures identified through clinical records and study database	12 mo after diagnosis
	Proportion of participants alive at 12 mo after diagnosis^f^	Follow-up conducted by PCs and entered in study database	Biological, imaging, and clinical procedures identified through clinical records and study database	12 mo after diagnosis
	Proportion of participants with recurrent disease^f^	AYA^h^ living with HIV and cancer who experience cancer recurrence	Biological, imaging, and clinical procedures identified through clinical records and study database	36 mo
	Proportion of participants adherent to ART^i^ and viral load	Prescription filled every 3 to 6 mo; blood test	Biological, imaging, and clinical procedures identified through clinical records and study database	Annually

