**HIV status, demographics, mediating outcomes, intervention dose, and clinical services**				
	HIV status and diagnosis date	Perinatally or behaviorally infected; CD4 count	Clinic record	Baseline
	Demographics and socioeconomic status	Research Triangle Institute AYA Zambia survey	Self-report	Baseline
	Self-efficacy (AYA living with HIV)	Generalized self-efficacy Scale [69]	Self-report	Baseline and 12, 24, and 36 mo
	Social support and mental health (AYA living with HIV)	Brief social support and patient health questionnaires [69,70]	Self-report	Baseline and 12, 24, and 36 mo
	HIV and cancer stigma (AYA living with HIV)	Anticipated stigma measures [71,72]	Self-report	Baseline and 12, 24, and 36 mo
	Cancer risk (AYA living with HIV)	Updated Research Triangle Institute cancer survey	Self-report	Baseline and 12, 24, and 36 mo
	Group education and sessions (AYA living with HIV)	Number and proportion of education sessions attended (dose)	PC tool; study database	12, 24, and 36 mo
	One-on-one education (AYA living with HIV)	Number of women receiving each level of strategy (dose)	PC tool; study database	12, 24, and 36 mo
	HIV and cancer team training (health care provider)	Proportion who attended initial training sessions (dose)	PC tool; study database	12, 24, and 36 mo
	Network meetings (health care provider)	Number and proportion of meetings attended (dose)	PC tool; study database	12, 24, and 36 mo
	Clinical team knowledge, confidence in ability, and collaboration (health care providers)	Survey on skills and patient communication; stigma related to AYA living with HIV (modified Nyblade instrument [73]) and peer learning and coordination	Self-report	Baseline and annually
	Diagnostic procedures by cancer type	Number of supplemental and diagnostic tests conducted	Clinical record	12, 24, and 36 mo
	Treatment modality by cancer type	Chemotherapy sessions; surgery; type of radiation	Clinical record	12, 24, and 36 mo

^a^KS: Kaposi sarcoma.

^b^NHL: non-Hodgkin lymphoma.

^c^CC: cervical cancer.

^d^PC: peer counselor.

^e^CD4: cluster of differentiation 4.

^f^Among AYA living with HIV and diagnosed with cancer.

^g^NHL stage based on the Lugano classification, CC stage based on the International Federation of Gynecology and Obstetrics, and KS stage based on the AIDS Clinical Trial Group system.

^h^AYA: adolescents and young adults.

^i^ART: antiretroviral therapy.

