**Future expansion**			
	Scale-up cost	To estimate the cost of large-scale implementation	Fixed versus variable activity-based cost estimates of implementation strategies to project economies of scale

Our main goal is to estimate the implementation cost from the program perspective. We will estimate labor hours by prospectively tracking time spent by each project staff member, including PCs, on a predefined set of activities (individuals will report their time monthly) and use hourly wages to calculate cost. We will capture time spent by health care providers, administrators, and policy makers participating in the ARROW Network and Collaborative using from the meetings. We will also document the expenditures on nonlabor resources to produce education materials, hosting group education sessions, the ARROW Provider Network meetings, and the cost of providing travel support. Using activity-based costing, we will allocate separate costs for supporting early diagnosis services and treatment adherence.

On the basis of these cost estimates and the primary end points from the trial, we will conduct incremental cost-effectiveness analysis by generating the cost per AYA living with HIV undergoing early detection services (physical examinations for KS and NHL and screening for CC) and the cost per AYA living with HIV and cancer completing recommended treatment modalities. Using standard economics methodology, we will explore economies of scale related to the implementation costs that can be achieved during scale-up [77,78]. We will also assess the key drivers of the cost of the ARROW program.

Using the trial data on estimated shift in stage at diagnosis and treatment adherence rates, along with supplemental information on prevalence of KS, NHL, and CC and mortality by stage at diagnosis, we will estimate the projected difference in mortality between ARROW and one-time education for AYA living HIV in Zambia. For CC screening, we will also estimate the incremental change in mortality using a validated microsimulation model, as screening not only will identify CC at an early stage but also can prevent CC by treating precancerous lesions [79,80].

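### The early-stage share is taken among diagnosed participants only and pooled over three cancers, so ARROW can move it through detection, prevention or cancer mix without a matching change in late-stage cancers

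*Protocol article*

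**What the plan says.** Study End Points, Early Detection Cohort, defines the secondary end point at 36 months as "the proportion of those diagnosed at an early stage (among those diagnosed with KS, NHL, and CC"). The same section expects few cancer cases and calls the findings inconclusive for that reason.

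Table 2 carries the end point as a single row. Early stage is defined separately for each cancer, "Stage 1 or 2 for NHL and CC; good risk for KS", and footnote f fixes the denominator: "Among AYA living with HIV and diagnosed with cancer". No rate of late-stage diagnosis per enrolled participant is defined. Analysis of Hypotheses applies intent-to-treat to the primary and secondary end points and leaves differences by cancer type to exploration.

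Sample Size and Recruitment, Early Detection Cohort, plans for ARROW to raise examination uptake from 15% to 35% and CC screening from 20% to 40% ("CC screening (40% in the ARROW arm) with over 85% power").

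Cost-Effectiveness and Return-on-Investment Scenarios projects the mortality difference "Using the trial data on estimated shift in stage at diagnosis and treatment adherence rates", together with outside figures on the prevalence of the three cancers and on mortality by stage. A microsimulation is added for CC because screening "will identify CC at an early stage but also can prevent CC by treating precancerous lesions". The section then derives a cost per life year saved for the three cancers combined.

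**The concern.** A share among diagnosed participants is a randomised comparison only if the arms diagnose cancers in the same way. Here the intervention is intended to change diagnosis, so membership of the denominator is itself an outcome of the arm. Three mechanisms follow.

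- **Extra early cases.** They enter both numerator and denominator and raise the share, even if the number of late-stage cancers is unchanged.
- **Prevention of CC.** Prevented cases leave the denominator. If CC is more often found early than the other two cancers, the share falls although patients have benefited.
- **Cancer mix.** The three cancers have different staging systems and probably different early-stage fractions. A change in mix moves the pooled share with no change within any cancer.

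The stated caveat about few cases concerns precision. The problem here is bias, which would remain with any number of cases. At stake is the reading of the secondary end point and, if the share is used there, the projected deaths, life years and return on investment.

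**Working it through.** The article gives no expected case count, effect size or power for this end point, so there is no figure to reproduce. The check is arithmetic on **assumed** case counts, early-stage fractions and stage mortality. From the article come the enrolled numbers (Results: 1731 ARROW, 1711 control) and, borrowed for illustration, the treatment cohort's target mix (CC 50%, KS 30%, NHL 20%).

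**1. Extra early cases, late cases fixed.** Share = early / (early + late).

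- Control: 8 early, 12 late: 8/20 = 40%.
- ARROW: 16 early, 12 late: 16/28 = 57%.
- With 4 extra early cases: 12/24 = 50%. With 12 extra: 20/32 = 62.5%.

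If the control share is s and the extra early cases are a fraction x of the control total, the new share is (s + x)/(1 + x), whatever the total. From s = 40%, x = 25%, 50% and 100% give 52%, 60% and 70%. From s = 30% they give 44%, 53% and 65%; from s = 50%, 60%, 67% and 75%.

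**2. The same data per enrolled participant.**

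- Late-stage: control 12/1711 = 7.01 per 1000; ARROW 12/1731 = 6.93 per 1000. The gap is only arm size.
- Early-stage: control 8/1711 = 4.68 per 1000; ARROW 16/1731 = 9.24 per 1000.

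The two rates show what happened: more early cases, no fewer late ones. The share alone does not.

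**3. Mix alone.** Assume early-stage fractions of CC 55%, KS 40% and NHL 20% in both arms. Pooled share = sum of (mix × fraction).

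- 50/30/20: 0.275 + 0.120 + 0.040 = 43.5%
- 60/25/15: 0.330 + 0.100 + 0.030 = 46.0%
- 70/20/10: 0.385 + 0.080 + 0.020 = 48.5%
- 40/36/24: 0.220 + 0.144 + 0.048 = 41.2%

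The last mix is what results if one third of CC is prevented and the rest is unchanged: starting from 100 cases, CC falls from 50 to 33.3, and 33.3/83.3 = 40%. Late-stage cases then fall from 22.5 + 18 + 16 = 56.5 to 15 + 18 + 16 = 49, a 13% reduction, while the share **falls** from 43.5% to 41.2%.

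**4. If the share were the projection input.** Deaths per case = share × early mortality + (1 − share) × late mortality, with assumed mortality of 20% early and 60% late.

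- Control: 0.40 × 0.2 + 0.60 × 0.6 = 0.44.
- ARROW in step 1: 0.571 × 0.2 + 0.429 × 0.6 = 0.371.
- Apparent reduction: 1 − 0.371/0.44 = 16%. With 4 to 12 extra early cases it is 9% to 20%.
- With early/late mortality of 10%/50%, 20%/60% or 30%/50% and the share rising from 40% to between 52% and 70%, apparent deaths averted run from 2.4 to 12.0 per 100 cases (6% to 35%).

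**5. The late-stage rate has its own weakness.** Assume 16 true late-stage cancers in each arm by 36 months, all found under ARROW but 12 in control. The rates are 16/1731 = 9.24 and 12/1711 = 7.01 per 1000, so ARROW looks about one third worse with no true difference.

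**The case against.** Several points on the other side are sound.

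- A reader might infer that the pooled share is the quantity multiplied by mortality by stage. The article does not say so. It refers to "Using the trial data on estimated shift in stage at diagnosis" and combines this with adherence and outside data, which leaves room for a projection by cancer. That would remove the mix problem. It would not remove the extra-early-cases problem, since a share within one cancer behaves as in step 1.
- The CC microsimulation partly handles prevention. It supplements the projection, covers CC only, and does not alter the end point.
- A reader might infer that a higher share with unchanged late-stage counts is a false signal. That goes too far. Early cases found by 36 months may be cancers that would have presented late afterwards, so the higher share is ambiguous.
- A reader might infer that the late-stage rate should replace the share. Step 5 shows why it should not: that rate also depends on detection.
- The end point is secondary, has no power claim and is labelled inconclusive, and the economic section plans sensitivity analyses over a range of effectiveness. This limits the weight of the point. Neither safeguard addresses the denominator.

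Details of the projection model may stand in a fuller plan. The denominator is not such a detail: the article fixes it in the text and again in Table 2.

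**Conclusion.** The concern holds in a limited form. As defined, the stage end point compares the arms within a group that the intervention helps to form, pooled over three cancers. Followed exactly, the plan can show a rise from 40% to 57% with no late-stage cancer avoided, or a small fall (43.5% to 41.2%) while late-stage cancers drop by 13%. These sizes rest on assumed counts and fractions; the mechanism does not.

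The share is the only stage measure defined for the projection, so the risk reaches the mortality and cost results, but its use there is a natural reading and not a stated fact. The 6% to 35% range of apparent mortality reduction applies only if the share is used in that way and none of the extra early cases averts a later late-stage one. No primary end point is affected. The change is worth making before the 36-month analysis.

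**What to change.** - At 36 months, report early-stage and late-stage diagnoses, by the Table 2 cut-offs, per enrolled participant, by arm and by cancer type. Analyse them with the clustered methods already planned, because 18 facilities were randomised and the 3442 participants were enrolled within them.
- Keep the early-stage share, but interpret it only beside these rates.
- In the mortality projection, use cancer-specific inputs. Do not read a higher share as a shift in stage unless the late-stage rate per enrolled participant supports it. Add a sensitivity analysis based on that rate.
- State that the caveat on this end point covers the changing denominator as well as the small numbers.

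**Cost.** No new data collection: stage, cancer type and enrolment are already to be recorded. Events by cancer type will be few and intervals wide. Late-stage counts may rise under ARROW through better detection by 36 months, so neither the share nor the late-stage rate should be read alone.

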##### Cancer Treatment Cohort

The primary end point is the proportion of those who are adherent to cancer treatment (complete all treatment modalities as prescribed; 2-week delays will be allowed) at 12 months after diagnosis, the secondary end point is the proportion alive at 12 months after diagnosis, and the tertiary end point is the proportion with recurrence at 24 and 36 months (among those with 24- and 36-month follow-up).

For all the AYA living with HIV, we will report adherence to ART (proportion of those filling prescriptions at least every 3 to 6 months) and viral load at 12, 24, and 36 months. Viral load testing is generally conducted at least annually for AYA living with HIV as part of routine guideline-recommended practice. We will reinforce the need for regular viral load testing as part of health care provider training and have set aside funds to conduct viral load testing for study participants for whom this information is unavailable in the medical record.

#### Sample Size and Recruitment

##### Early Detection Cohort

We will use stratified random sampling to select an equal number of male and female participants and a mix of AYA living with HIV with perinatally and behaviorally acquired HIV. In terms of age distribution, 20% (720/3600) of the sample will be aged 15 to 19 years, 20% (720/3600) will be aged 20 to 24 years, and 60% (2160/3600) will be aged 25 to 39 years. We will oversample AYA living with HIV in each stratum to account for AYA living with HIV who may not meet inclusion criteria or who decline to participate. HIV facility staff will contact AYA living with HIV or consenting adults (for those aged 15 to 17 years) to discuss the study, and those interested will meet with trained data collectors who will assess eligibility and obtain consent or assent. The sample size was calculated assuming conventional specifications (α=.025 for each end point, 2-sided tests) based on the dual primary end points and allowing for the detection of an absolute 20% point improvement in the primary end points, which is our minimum threshold to consider the ARROW program successful. For the one-time education arm, given the current low level of uptake of early diagnosis services, we estimate uptake of physical examinations to be about 15% (15/100) and CC screening to be about 20% (20/100) at 12 months. With our proposed sample size of 3600, we will be able to detect a 20% difference in uptake of physician examination (35% in the ARROW arm) with over 90% power and CC screening (40% in the ARROW arm) with over 85% power. We can achieve this even after accounting for up to 10% attrition at 12 months (a previous study conducted by the research team achieved this retention rate without the level of active participant contact planned for this study) [67]. We estimate that the interclass correlation coefficient will be in the range of 0.03 to 0.05 because correlation coefficients for binary data are typically quite small, especially when physical examinations and screening uptake are very low [68].

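### The early detection cohort's dual primary end points differ between the end point and sample size sections, so the alpha split does not fit the listed proportions and the second primary has no power basis

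*Protocol article*

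**What the plan says.** Under Study End Points, Early Detection Cohort, the Protocol article names two primary end points.

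- First: "The first primary end point is the proportion of those who complete a physical examination visit for KS and NHL", together with the proportion of "those who are up to date with CC screening (female participants only) at 12 months". That is two proportions, one in all participants and one in women only.
- Second: "The second primary end point is the proportion of those who complete the recommended follow-up supplemental or diagnostic procedures" within 3 months of referral, then "those who initiate cancer treatment (within 3 months of diagnosis), and those who complete additional cancer detection visits over 36 months". That is three more proportions.

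Under Sample Size and Recruitment, Early Detection Cohort, the alpha is set as follows: "The sample size was calculated assuming conventional specifications (α=.025 for each end point, 2-sided tests) based on the dual primary end points", with a 20-point absolute improvement as the threshold for the primary end points in general. Control rates follow for two proportions only: 15% for examination and 20% for cervical screening at 12 months. The power statement covers the same two: the trial is said to "detect a 20% difference in uptake of physician examination (35% in the ARROW arm) with over 90% power and CC screening" (40% against 20%) with over 85% power. Both allow for 10% attrition at 12 months, and the intracluster correlation is put at 0.03 to 0.05.

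Table 2 marks examination and cervical screening as the primary end point at 24 months. It times diagnostic completion and treatment initiation at 24 and 36 months, and repeat examination and screening at 36 months. Analysis of Hypotheses mentions the dual primary end points without saying how components are combined.

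**The concern.** The two sections appear to mean different pairs by dual primary. In the end point section the pair is (examination plus cervical screening) and (follow-up, treatment initiation, repeat visits). In the sample size section the pair that is actually powered is examination and cervical screening, which together make up only the first of those.

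Two things are at stake. First, an alpha of .025 for each end point cannot be mapped onto tests. Two end points use up .05, but five proportions are listed and nothing says how many tests they generate. Second, the sample size is said to rest on both primaries, yet nothing in the calculation bears on the second. A reader of the final report could not tell which results carry a confirmatory claim.

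**Working it through.** **Inputs (Protocol article).** 18 facilities, 9 per arm; 200 participants per facility, of whom 100 are women; 10% attrition, leaving m = 180 (examination) or m = 90 (women, cervical screening) per facility; intracluster correlation 0.03 to 0.05; two-sided alpha .025; 15% v 35% and 20% v 40%.

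**Step 1: reproduce the stated powers.** Effective n per arm = 9m / [1 + (m − 1) × ICC].

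- Examination, ICC 0.05: 1 + 179 × 0.05 = 9.95; 1620 / 9.95 = 162.8.
- Cervical screening, ICC 0.05: 1 + 89 × 0.05 = 5.45; 810 / 5.45 = 148.6.

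Power by the normal approximation is Φ{[d − z × √(2p̄(1 − p̄)/n)] / √[(p₁(1 − p₁) + p₂(1 − p₂))/n]}, with d = 0.20 and z = 2.241.

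- Examination: (0.20 − 2.241 × 0.0480) / 0.0467 = 1.98, so 97.6%.
- Cervical screening: (0.20 − 2.241 × 0.0532) / 0.0519 = 1.56, so 94.0%.

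With a noncentral t on 16 degrees of freedom, to respect 18 clusters, the figures are 95.5% and 90.4%. At ICC 0.03 the normal approximation gives 99.9% and 99.2%. The stated figures (over 90% and over 85%) hold as lower bounds.

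**Step 2: what the calculation covers.**

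| Proportion | Primary end point | Denominator | Control rate | Power |
|---|---|---|---|---|
| KS/NHL examination | first | all | 15% | over 90% |
| Cervical screening | first | women | 20% | over 85% |
| Follow-up procedures | second | those referred | none | none |
| Treatment initiation | second | those diagnosed | none | none |
| Additional detection visits | second | not stated | none | none |

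No power can be computed for the last three rows. The 20-point threshold covers them nominally, but without a control rate and denominator it gives no power. Attrition is stated only to 12 months, while the second end point runs to 36. The end point section itself expects few cancers, and these are the denominator for treatment initiation.

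**Step 3: family error by number of tests at .025.** The bound is k × .025; under independence it is 1 − 0.975^k. The correlated columns come from simulating equicorrelated test statistics.

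| Tests | Bound | Independent | Correlation 0.5 | Correlation 0.8 |
|---|---|---|---|---|
| 2 | 5.0% | 4.9% | 4.7% | 4.0% |
| 3 | 7.5% | 7.3% | 6.6% | 5.1% |
| 5 | 12.5% | 11.9% | 9.8% | 6.8% |

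Three tests would arise if the first end point were tested as two proportions and the second as one composite.

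**Step 4: if the first end point's .025 is shared (.0125 each).** At ICC 0.05 with attrition, examination has 95.7% (normal) or 91.2% (t, 16 df), and cervical screening 90.3% or 83.5%. The stated figure of over 85% for cervical screening would then depend on the method used.

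**The case against.** The strongest reply is that the article names two end points and gives .025 to each, so the literal total is .05. If each end point is a single composite, or all its components must succeed, error is controlled; and a combination rule is something an article may leave to the full protocol or analysis plan. This stands in part. A reader might infer that the plan as written has a 12.5% error rate, but the documents do not support that: nowhere do they say that each of five proportions gets its own .025 or that any one suffices for success. The inflation is conditional, and 12.5% is an upper bound. The outcomes are measured in overlapping people within the same clusters, so positive correlation, and hence a smaller figure, is plausible.

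Three other tempting readings also go too far.

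- The article's warning of inconclusive findings concerns the secondary end point of stage at diagnosis, not treatment initiation. Only its reason, the small number of cancers, carries over, and by inference.
- The second primary is not wholly without an effect size, since the 20-point threshold is stated for the primaries in general. Nor are all its components sparse: Table 2 describes additional visits as repeat examination and screening, which is not confined to diagnosed cases.
- The sample size is not shown to be wrong; Step 1 confirms the two powers given.

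What the reply does not remove is the mismatch inside the article. If the alpha split refers to examination and cervical screening, the second primary has no alpha. If it refers to the two end points as defined, the second has .025 but no power basis, and the first has one .025 for two separately powered proportions.

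**Conclusion.** The point holds as a contradiction between two sections of the same article, not as a detail left to an analysis plan. The alpha split and the claim that the sample size rests on both primaries do not match the end points as defined. Power is stated, correctly, for two of five proportions; for the other three it cannot be derived. Family error stays at 5% under a composite or all-must-succeed rule, and rises to between about 7% (correlation 0.8) and 12.5% (bound) if all five are tested separately at .025. Which applies cannot be told from the text. The conflict between 12 and 24 months for the first end point adds to the ambiguity. It should be settled now: 12-month results are scheduled for early 2026, and choosing primaries after seeing them would be data-driven.

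**What to change.** Before any 12-month result is seen, amend the protocol, with matching wording in the registry entry and analysis plan:

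1. Name two primary end points, each at two-sided .025: KS/NHL examination in all participants, and up to date with cervical screening in women. This matches the existing sample size calculation. It also matches the cost-effectiveness section, which draws on the primary end points and costs these same early detection services.
2. State one primary time point, reconciling 12 months in Study End Points with 24 months in Table 2.
3. Make follow-up completion, treatment initiation and additional detection visits key secondary, tested in a fixed order with only the alpha released by rejected primaries: .025 if one succeeds, .05 only if both do. The level must be written down. Testing at .05 after either success would allow an error of 1 − 0.975 × 0.95 = 7.4% (assuming independence) when one primary is effective and is rejected, and the other primary and the first secondary are null.

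If the second primary is kept instead, say that the sample size and power statement does not cover it, and state for each end point a composite or all-must-succeed rule that holds it at .025. For the first end point an all-must-succeed rule is affordable: joint power is at least 95.5% + 90.4% − 100% = 85.9% at ICC 0.05 (t, 16 df). For the second it would be limited by its weakest component, and treatment initiation rests on few cases.

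The cost is an amendment and consistent wording. No extra participants or data are needed. The downside is that the later outcomes lose the primary label.
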